## **10. ETHICAL CONSIDERATIONS**

### **10.1. Regulation statement**

The study will be conducted according to the principles of the Declaration of Helsinki (59th WMA General Assembly, Seoul, October 2008) and according to the latest revised version of the Medical Research Involving Human Subjects (WMO). The procedures set out in this study protocol are designed to ensure that the sponsor and investigator abide by the principles of the GCP guidelines of the European Community (ICH topic E6, CPMP/ICH/135/95, Directive 2001/20/EC) and the Declaration of Helsinki (in the latest revised version) in the conduct, evaluation and documentation of this study. Copies of the ICH-GCP-Guidelines and the Declaration of Helsinki are included in the Investigator's Study File.

The protocol has to be approved by the Medical Ethical Committee of the local Hospital before a patient can enter the study.

### **10.2. Recruitment and consent**

All GBS patients admitted to the participating hospitals will be asked to participate in this study by their treating neurologist or PI. He or she will inform the patients about the study using the patient information letter. We developed a special patient information letter for children of 12-17 years of age. Contact information of the researchers and the independent physician is given in the patient information letter and intended participants are encouraged to contact them. All patients will be given opportunity to ask questions and allowed sufficient time to consider the information provided. The patient's signed and dated informed consent will be obtained and filed before conducting any procedure specifically for the study. The investigators will store the original, signed informed consent form. A copy of the signed informed consent form will be given to the patient.

### **10.3. Objection by minors or incapacitated subjects**

Objection by minors or incapacitated will be dealt with in conformity with the code of conduct 'Gedragscode bij verzet van minderjarigen die deelnemen aan medisch-wetenschappelijk onderzoek' (in English; code of conduct in case of objection by minors taking part in medical research). This code of conduct was accepted on May 21, 2001 by a conference of the Board of the Dutch Society of Paediatrics (Nederlandse Vereniging voor Kindergeneeskunde, NVK) and is published on the website of the CCMO (Dutch Competent Authority). When a trial participant objects against any act he or she is submitted to according the trial protocol the study should not take place in that particular participant (WMO, art. 4, lid 2). In conference with the parents or caretakers an assessment is made about suspected reactions in the child. Possible objection of the minor and which behaviour is defined as objection will be discussed with the parents or caretakers of the minor. Code of conduct in case of objection of the individual minor will be indicated.

#### **10.4. Benefits and risks assessment, group relatedness**

Benefit of IVIg in GBS patients, who were unable to walk unaided and who were started on IVIg within the first 2 weeks after onset of weakness, is clearly demonstrated and IVIg is at present the standard treatment in GBS[6, 33]. Very limited information is available concerning the optimal dosage of IVIg. For reasons described earlier we expect benefit of a second dosage IVIg in patients with poor prognosis; however this has never been proven. IVIg treatment is usually well tolerated; minor side effects can include headache, chest pain, myalgia, nausea, or fatigue presumably mediated by the release of pro-inflammatory cytokines in susceptible patients. Many of these symptoms are easily managed by slowing down the infusion rate or the use of co-medication with non-steroidal antiphlogistics. Severe complications are rare and include arterial or venous thrombosis (such as pulmonary embolism, stroke, and myocardial infarction), anaphylaxis, most likely in the case of allergic or hereditary IgA deficiency (which is a contra-indication for IVIg therapy and consequently for this study); and renal disturbances, that rarely has been described in patients already known with insufficient renal function. A second IVIg course theoretically can have side-effects due to the load of protein and increased blood viscosity. Finally IVIg is expensive and there appears to be a potential world-wide shortage. More intensive treatment applied in a targeted population has advantage both from a medical and socio-economical point of view.

#### **10.5. Compensation for injury**

The investigator has a liability insurance which is in accordance with article 7, subsection 6 of the WMO. The sponsor (also) has an insurance which is in accordance with the legal requirements in the Netherlands (Article 7 WMO and the Measure regarding Compulsory Insurance for Clinical Research in Humans of 23th June 2003). This insurance provides cover for damage to research subjects through injury of death caused by the study.

1. €450.000,-- (i.e. four hundred and fifty thousand Euro) for death or injury for each subject who participates in the research;
2. €3500.000,-- (i.e. three million five hundred thousand Euro) for death or injury for all subjects who participate in the research;
3. €5.000.000,-- (i.e. five million Euro) for the total damage incurred by the organisation for all damage disclosed by scientific research for the sponsor as 'verrichter' in the meaning of said Act in each year of insurance coverage.

The insurance applies to the damage that becomes apparent during the study or within 4 years after the end of the study.

## **11. ADMINISTRATIVE ASPECTS AND PUBLICATION**

### **11.1. Handling and storage of data and documents**

When a GBS patient is included in the study he or she will be assigned a unique number. Name, address and date of birth will be stored separately from the study data. Data will be recorded on CRFs and entered in the database twice to prevent data entry faults. The database will contain rules to prevent the entry of invalid data. Data will be entered regularly to prevent missing data being overlooked. Independent monitoring will be established to ensure that the study is conducted, recorded and reported in accordance with the protocol and GCP. The investigators, members of the Health Inspection and members of the Medical Ethical Committee have access to personal data. Research data will be handled with due observance of the Dutch Law for Protection of Personal data (Wet Bescherming Persoonsgegevens) and the privacy statement of the Erasmus MC. With informed consent research data will be stored during 15 years. Human material will be stored non-traceable for 15 years, when informed consent is obtained. We expect that the stored material will be very valuable for future research.

### **Study Monitoring**

Sanquin Plasma Products has developed monitoring and auditing procedures. Monitors or delegates of Sanquin Plasma Products will monitor the site, in order to comply with GCP guidelines. For this study, the expected average monitoring frequency is 6 months, or more frequent, if necessary, by personal visit. The pharmacy will be visited once a year or more frequent, if necessary. The hospital laboratory will be visited when required. Checking of the CRFs for completeness and clarity, and cross-checking with source documents in the presence of the investigator - giving due consideration to data protection and medical confidentiality - will be required, and the investigator assures Sanquin Plasma Products of support at all times. This will be necessary to monitor the progress of the study. The regulatory authorities and/or the sponsor's Clinical Quality Assurance Group may also wish to carry out such source data checks and/or inspections/audits.

### **11.2. Amendments**

A 'substantial amendment' is defined as an amendment to the terms of the METC application, or to the protocol or any other supporting documentation, that is likely to affect to a significant degree:

- The safety or physical or mental integrity of the subjects of the trial;
- The scientific value of the trial;
- The conduct or management of the trial; or
- The quality or safety of any intervention used in the trial.

All substantial amendments will be notified to the METC and to the competent authority. Non-substantial amendments will not be notified to the accredited METC and the competent authority, but will be recorded and filed by the sponsor.

### **11.3. Annual progress report**

The sponsor / principal investigator will submit a summary of the progress of the trial to the accredited METC once a year. Information will be provided on the date of inclusion of the first subject, numbers of subjects included and numbers of subjects that have completed the trial, serious adverse events/serious adverse reactions, other problems and amendments.

### **11.4. End of study report**

The sponsor / principal investigator will notify the accredited METC and the competent authority of the end of the study within a period of 90 days. The end of the study is defined as the last patient's last visit. Inclusion of patients will stop after 44 patients eligible for a second dosage IVIg have been included.

In case the study is ended prematurely, the sponsor will notify the accredited METC and the competent authority within 15 days, including the reasons for the premature termination.

Within one year after the end of the study, the investigator/sponsor will submit a final study report with the results of the study, including any publications/abstracts of the study, to the accredited METC and the Competent Authority.

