### 3. STUDY DESIGN

A double-blind randomized placebo-controlled trial design will be used in selected patients with a poor prognosis. In patients with a good prognosis the study will have an observational design.

- All GBS patients in need of IVIg treatment, according to the treating neurologist, in a standard dosage of 2 g/kg in 2-5 consecutive days are potentially eligible for this study after obtaining informed consent.
- When patients sign 'Informed consent' they principally agree to be randomized to get a second IVIg dose or placebo when having a poor prognosis at day 7 and to be followed up for 6 months.
- Patients with the poorest prognosis based upon the modified EGOS (mEGOS 6-12) after the first IVIg course will be randomized to get a second course of IVIg (Nanogam®) in a dosage of 8 ml/kg (=0,4 g/kg) for 5 days or placebo (GPO®) in a dosage of 8 ml/kg for 5 days in a blinded fashion.
- mEGOS must preferentially be assessed 7 days after start of first IVIg course, with a range to 8 or 9 days. Trial medication needs then to be started within 24 hours when indicated according to the mEGOS score (see figure 4).
- Patient follow-up will be 6 months.
- Total patient inclusion will end when 44 patients with a poor prognosis received a second IVIg dosage.
- After covariate adjustment, to deal with variation between patients in baseline risk and to increase statistical power, data of the placebo group and the intervention group will be compared.

This is shown in the flowchart (table 2).

[figure not shown]

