### **4.4. Sample size calculation**

- We will select patients with poorest prognosis (mEGOS 6-12), this corresponds with approximately 50% of the population.
- Calculations showed that the prognosis of this group (mEGOS 6-12) is poor both at 4 weeks (85% unable to walk unaided) and at 26 weeks (35% unable to walk unaided).
- We presume that a second dose of IVIg in patients with poor prognosis (mEGOS 6-12) will raise the percentage of patients improving on the GBS disability score at 4 weeks with 15-25%. For power analysis for our primary outcome we used an improvement of 20%.
- Assuming a 20% improvement in unadjusted data and with a dichotomous outcome (being able to walk unaided versus being unable to walk unaided) we will need ( $\alpha=0.05$  and power=0.80) 290 patients in total (145 poor and 145 good prognosis).
- The power increase through covariate adjustment and the use of the ordinal outcome may be expected to result in a reduction in required sample size of 40 to 50% [31]. This leads to a required sample size of 60% of 290 patients = 174 patients.
- Based on previous calculations 50% of 174 patients (n=87) will have a poor prognosis. This group of 87 patients will be randomized to receive a second course of IVIg (n=44) or placebo (n=44).
- We expect that a sample size of 174 patients is well feasible with approximately 3 years of accrual.

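### Section 11.4 ends inclusion at 44 patients eligible for a second course; read literally that is about 22 per arm, half the size planned in section 4.4, with power of about 51% instead of 80%

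*Protocol*

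**What the plan says.** Two sentences in the protocol say when inclusion ends.

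- Section 11.4 (End of study report): "Inclusion of patients will stop after 44 patients eligible for a second dosage IVIg have been included".
- Section 3 (Study design): "Total patient inclusion will end when 44 patients with a poor prognosis received a second IVIg dosage".

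The planned size is set elsewhere. Section 4.4 says: "This group of 87 patients will be randomized to receive a second course of IVIg (n=44) or placebo (n=44"). Section 4.1 also expects 87 randomised patients, and section 9 plans to compare 44 IVIg patients with 44 placebo patients.

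The conditions for entering the randomised phase are in section 4.2 B: a first Nanogam course started within two weeks of onset, given at the stated total dose, and mEGOS 6-12 at day 7. All of these are known before allocation.

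**The concern.** A patient eligible for the second course is any patient who meets section 4.2 B, whichever arm allocation then gives. Forty-four such patients are 44 randomised patients in total, not 44 per arm. Section 11.4 therefore sets the end of inclusion at half of what section 4.4 requires, in the section that defines the end of the study.

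Whoever applies the protocol cannot satisfy both texts. Stopping at 44 eligible patients abandons the sample size calculation, and going on departs from section 11.4. What is at stake is the power for the primary endpoint, the GBS disability score at 4 weeks.

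**Working it through.** **Inputs, all from section 4.4 unless marked**

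- Control rate: the prognosis "is poor both at 4 weeks (85% unable to walk unaided"), so 15% walk unaided.
- Effect: "For power analysis for our primary outcome we used an improvement of 20" per cent, read as percentage points, so 35% walk unaided with a second course.
- α = 0.05 "and power=0.80". Sidedness is not stated. Two-sided is assumed, because it reproduces the protocol's figure.
- Unadjusted binary size: "290 patients in total (145 poor and 145 good prognosis").
- Saving from covariate adjustment and the ordinal outcome: a "reduction in required sample size of 40 to 50" per cent; the protocol applies 40%.

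**Step 1: reproduce the protocol's figure**

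n per arm = [z(0.975)·√(2p̄(1−p̄)) + z(0.80)·√(p₁(1−p₁) + p₂(1−p₂))]² / (p₂−p₁)², with p₁ = 0.15, p₂ = 0.35, p̄ = 0.25.

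- z(0.975)·√0.375 = 1.960 × 0.6124 = 1.2002
- z(0.80)·√0.355 = 0.8416 × 0.5958 = 0.5015
- n = (1.2002 + 0.5015)² / 0.04 = 72.4 per arm, 144.8 in total

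This agrees with the stated 145 poor-prognosis patients. A one-sided test would need 57 per arm (114 in total), which does not agree. With the 40% saving, 0.60 × 145 = 87, as stated; 44 per arm makes 88.

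**Step 2: size under section 11.4 read literally**

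44 eligible patients allocated 1:1 give 22 per arm. That is 44/88 = 50% of the planned randomised sample.

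**Step 3: power on the protocol's own basis**

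Power = Φ{[0.20·√m − 1.2002] / 0.5958}, where m = n / (1 − saving) is the effective number per arm.

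| Patients per arm | Saving | m | Power |
|---|---|---|---|
| 44 | 40% | 73.3 | Φ(0.860) = 80.5% |
| 22 | 40% | 36.7 | Φ(0.018) = 50.7% |
| 44 | 50% | 88 | Φ(1.134) = 87.2% |
| 22 | 50% | 44 | Φ(0.212) = 58.4% |
| 22 | none | 22 | Φ(−0.440) = 33.0% |

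A check that does not use the saving: halving the information of any design with 80% power gives Φ[(1.960 + 0.8416)/√2 − 1.960] = Φ(0.021) = 50.8%.

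**Step 4: proportional-odds check**

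The planned effect is an odds ratio of (0.35/0.65)/(0.15/0.85) = 3.05, with logarithm 1.116. By Whitehead's formula, power = Φ[1.116·√V − 1.960], with V = (N/12)(1 − s). Here s is the sum of the cubed mean proportions over the grades of the disability score. The protocol does not give the grade distribution, so s is an assumption; 0.07 to 0.15 is used.

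- N = 87: V = 6.74 to 6.16, power 83% to 79%
- N = 44: V = 3.41 to 3.12, power 54% to 50%

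The ordinal calculation gives the same picture as Step 3.

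**The case against.** The strongest reply is that section 11.4 is a slip and not a competing plan. Section 3 (44 who received IVIg), section 4.1 (87 randomised), section 4.4 (44 and 44) and section 9 (44 against 44, and 44 against the other 130 of 174) all point to 44 per arm. Section 11.4 looks like a looser repetition of the 44 in section 3. This is very probably right, and a sponsor working from section 4.4 would not stop at 44. It explains the error but does not remove it, because the sentence as written authorises a stop at half size.

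Some stronger readings are tempting but not supported:

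- *The protocol has three rival stopping rules.* Section 4.4 is a sample size calculation, not a stopping rule. Section 3 broadly agrees with it, since 44 IVIg patients at 1:1 means about 88 randomised.
- *The section 3 rule breaks the blind.* Section 7.2 blinds the coordinating investigator, co-investigator, local investigator, the manufacturer's trial coordinator and the patient. Pharmacists are not on that list and could keep the count. The protocol does not say who counts, so a breach is not shown.
- *Placebo patients given open IVIg for a treatment-related fluctuation count towards the 44.* This strains the wording. Section 7.2 calls that treatment an open course, while the second IVIg dosage elsewhere means the randomised course.
- *The section 3 rule seriously endangers power.* Blocks are per site and many sites may recruit few patients, so the placebo arm need not be exactly 44 when the 44th IVIg patient enters. A simulation with 67 sites of unequal size and blocks of 4 gave a 95% range of 32 to 56 placebo patients. The protocol states neither the block size nor the site sizes. Even over that range, power with the 40% saving is about 72 to 85%.

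**Conclusion.** The point holds as an internal contradiction in the size of the trial. Section 11.4, followed literally, ends the randomised comparison at about 22 per arm, against the 44 per arm in sections 4.4 and 9. Power at the planned effect then falls from 80% to about 51%. Across the protocol's own assumptions the figure at 22 per arm runs from 33% (unadjusted binary) to 58% (50% saving).

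This rests on a two-sided test, 1:1 allocation, the protocol's 15% and 35%, and its unverified saving from adjustment and ordinal analysis. The loss of half the information does not depend on the saving.

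A reader might infer that the sponsor intends to stop at 44 randomised. The rest of the protocol speaks against that, so the defect lies in the wording of the threshold. It should still be corrected, because the threshold decides when recruitment closes.

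**What to change.** Put one rule in sections 3 and 11.4 that matches section 4.4, for example: inclusion ends when 88 patients with mEGOS 6-12 have been randomised, both arms counted together and irrespective of the treatment received. In section 4.4, write 88 where the randomised group is given as 87, so that the total agrees with 44 per arm.

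A secondary benefit is that a count of all randomised patients needs no arm-level information. It fixes the total, where the count in section 3 fixes one arm of a blinded trial and leaves the other to per-site blocks.

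The cost is wording only. It restores the size that section 4.4 already plans, with at most one patient more than the stated 87.

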### **11.5. Public disclosure and publication policy**

This national trial will be conducted on behalf of the Dutch GBS study group. The results of this study will be published in the name of the SID-GBS study group. There will be a writing group, consisting out of the members of the Steering committee and researchers especially working on this study. Neurologists who include patients are members of the Dutch GBS study group, they will be listed as co-authors according to the numbers of patients included in their center.

Papers will be published conforming to CCMO guidelines. Any scientific communications drafted by the investigators should be sent to the Medical Department of Sanquin Plasma Products at least 30 days prior to submission to a scientific journal/meeting. Sanquin Plasma Products do not have the right to withhold the data from publication but can require changes with respect to issues regarding proprietary protection. If necessary, the authorities will be notified of the investigator's name, address, qualifications and extent of involvement. By signing the study protocol, the investigators agree with the use for publication and information for medical and pharmaceutical professionals.

## APPENDIX A

### Assessment scales

table 3: GBS disability score

| GBS disability score |                                                                                       |
|-----------------------------|---------------------------------------------------------------------------------------|
| 0                           | A healthy state                                                                       |
| 1                           | Minor symptoms and capable of running                                                 |
| 2                           | Able to walk 10 metres or more without assistance but unable to run                   |
| 3                           | Able to walk 10 metres across an open space with help (e.g. sticks, crutches, walker) |
| 4                           | Bedridden or chairbound                                                               |
| 5                           | Requiring assisted ventilation for at least part of the day                           |
| 6                           | death                                                                                 |

table 4: MRC sumscore

| MRC sumscore                                                                                                                                                                                                                                                                       |                                                              |
|-------------------------------------------------------------------------------------------------------------------------------------------------------------------------------------------------------------------------------------------------------------------------------------------|--------------------------------------------------------------|
| Sum of MRC scores from six bilaterally muscle groups, including shoulder abductors, elbow flexors, wrist extensors, hip flexors, knee extensors and foot dorsiflexors, ranging from 60 (normal strength) to 0 (quadriplegic). The MRC sum of an individual muscle ranges from 0-5: |                                                              |
| 0                                                                                                                                                                                                                                                                                         | No visible contraction                                       |
| 1                                                                                                                                                                                                                                                                                         | Visible contraction without movement of the limb             |
| 2                                                                                                                                                                                                                                                                                         | Active movement of the limb, but not against gravity         |
| 3                                                                                                                                                                                                                                                                                         | Active movement against gravity over (almost) the full range |
| 4                                                                                                                                                                                                                                                                                         | Active movement against gravity and resistance               |
| 5                                                                                                                                                                                                                                                                                         | Normal strength                                              |

table 5: Overall Neuropathy Limitations Scale

